| To estimate the uptake and increase in coverage associated with offering self-sampling              | 
1. Uptake of kits at 30 days, 90 days and at the end of the trial*
 
2. Change in coverage at participating GP practices (when additionally counting a negative HPV test on a self-sample as having been screened) from the start vs the end of the trial.
 
3. Change in the proportion eligible appropriately screened.
 | 
1. Uptake: number of women screened by self-sample (at 30 days and 90 days from date kit mailed out (from print company) or given out in GP practice (GP records), and total) (from NHAIS and central laboratory) as a % of all women sent kit or opportunistically offered kit (from NHAIS for 15m and from GP record data for opportunistic)
 
2. Coverage: Age-appropriate coverage (as determined by the number of women who have either been screened by cytology or HPV negative on a primary HPV test or self-sample in the past 3.5y if aged 25-49 or 5.5y if aged 50-64y as a % of all those eligible for cervical screening) at participating GP practices. The endpoint is the change in coverage from the (practice-specific) beginning to the (practice-specific) end of the trial (all NHAIS data).
 
3. Eligible women (on the first of each month): women not ceased from screening aged 25-49 who have not been screened within the last 2.9 years or aged 50-64 and not screened within the last 4.9 years.
Appropriately screened: number of eligible women screened within the month. Data will be collected separately for "conventional screen", "return of mailout kit" and "return of opportunistic kit". The proportion eligible screened (by any approach) will be recorded each month during the trial and for the four months before the trial start. The average for the before and after period will be compared.
 |

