### 4.2 Active recruitment

Active recruitment at each GP practice is planned for up to 12 months but may be longer or shorter depending on self-sampling uptake rates. Potentially, GP practices may recruit for longer if response rates are lower than expected or if further funds are made available to continue the intervention as part of service improvement (e.g. from NHS commissioners) and an amendment to extend the study recruitment period is approved.

In addition, if we find that the uptake of self-sampling is much lower than expected we may recruit additional GP practices. We will also do outreach at the CCG level to boost GP practice engagement and offering of opportunistic kits.

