### **7.10 End of Trial**

The end of the active recruitment of the trial will be defined as either when a minimum of 10,000 kits have been returned or at 12 months after study start, whichever is earliest.

The trial will end once a minimum of 6 months of follow-up data (6 months from the last participant recruited) for women testing HPV positive on a self-sample have been received.

The Chief Investigator will inform the REC of the end of the trial within 90 days of its completion. A summary of the final research report will be sent to the REC within 12 months of the end of the trial

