### 9.1.1 Direct Mail-out

Assuming 106 GP practices recruit women for an average of 9 months (GP practices will recruit for a minimum of 6 months and a maximum of 12 months given that study set-up at each practice will be staggered over a 6 month period) and 20 women reach the 15 month anniversary at each practice each month, approximately 19,000 women will be sent kits during the trial. Table 2 below provides the expected 95% confidence intervals for various uptake levels over an average of 9 months recruitment period. We have estimated that 15% of women who receive a kit via direct mail-out will return a self-sample (i.e. ~2,800 women will return a self-sample over an average of 9m).

**Table 2 Expected 95% confidence intervals for different proportions of women who return a self-sample based on 106 GP practices over a 9-month average recruitment period**

| Uptake among those offered kits | 95%CI     |
|---------------------------------|-----------|
| 10%                             | 9.6-10.4  |
| 15%                             | 14.5-15.5 |
| 20%                             | 19.4-20.6 |
| 30%                             | 29.3-30.7 |

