### 9.2.3 Secondary outcomes – GP practice level

Based on NHAIS data, we will explore change (before vs. after) in cervical screening coverage. We will explore variation across GP practice using Funnel plots.

We will run a Mantel-Haenszel test accounting for clustering at the GP practice level to explore the relationship between coverage and before/after.

We will also explore whether coverage varies as a function of age group, screening history, ethnic group and LSOA using change in cervical screening coverage using the extended Mantel-Haenszel test for 2\*j tables so to account for the clusters.

Change in cervical screening coverage at each practice (to assess the impact of self-sampling on coverage):

- Before (including both immediately before the GP practice is “entered” into the trial and exactly one year before the end of the trial) and after the trial.
- Coverage in each month prior to and post the trial starting at the GP practice.

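### Under the section 7.10 definition of trial end, the second baseline date for coverage in section 9.2.3 falls after kits have started at every practice recruiting for more than 6 months

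*Protocol*

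**What the plan says.** Section 9.2.3 of the protocol examines change in coverage at each practice. Its list of time points opens with "Before (including both immediately before the GP practice is “entered” into the trial" and then adds a second baseline, "exactly one year before the end of the trial) and after the trial". The next item asks for monthly coverage before and after the practice starts.

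Section 7.10 gives two separate closing points. Active recruitment stops "either when a minimum of 10,000 kits have been returned or at 12 months after study start, whichever is earliest". The trial closes later: "The trial will end once a minimum of 6 months of follow-up data (6 months from the last participant recruited". No other section defines the end of the trial.

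Section 3.2 defines primary endpoint 2 as the change in coverage "from the (practice-specific) beginning to the (practice-specific) end of the trial (all NHAIS data". That practice-specific end is not defined. The same entry counts an HPV-negative self-sample as coverage.

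On recruitment length, section 9.1.1 states: "GP practices will recruit for a minimum of 6 months and a maximum of 12 months". It attributes the spread to staggered set-up.

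**The concern.** A baseline should hold none of the intervention. Trial end lies at least 6 months beyond the close of recruitment, so stepping back 12 months from it does not reach back past the start of recruitment at most practices. The value labelled as before the trial would be measured while kits were already being mailed and handed out.

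Section 9.2.3 says this comparison is meant to assess what self-sampling does to coverage. With one clean and one partly exposed baseline, the plan would give two estimates that differ because of a date rule. The overlap grows with recruitment length, so it is greatest at the practices that start first. It could then be mistaken for real variation between practices in the funnel plots planned in the same section.

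**Working it through.** **1. The plan's own timeline.** At most 12 months of recruitment (7.10) plus 6 months of follow-up gives 12 + 6 = 18 months. This matches the 6 to 18 months of individual follow-up in section 4.3. The Trial Summary total also reproduces: 3 + 9 + 6 + 3 = 21 months. The sections therefore agree that trial end falls about 6 months after recruitment closes.

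**2. Inputs.**
- D, a practice's recruitment length: 6 to 12 months. The average is 9, from "Assuming 106 GP practices recruit women for an average of 9 months" (9.1.1).
- L, the time from close of recruitment to trial end: at least 6 months (7.10).
- Assumption: practices start at different dates and close together, as the staggered set-up in 9.1.1 implies. A practice closing before the others would have more of its recruitment ahead of the date.

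**3. Where the second baseline falls.** Counted from practice entry, trial end is month D + L. One year earlier is month D + L − 12, which for L = 6 is month D − 6. If returns accrue evenly, the share already in is (D − 6)/D.

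| D (months) | Baseline at practice month | Share already in, L = 6 | Share if L = 9 (assumed) |
|---|---|---|---|
| 6 | 0 | 0% | 3/6 = 50% |
| 9 | 3 | 3/9 = 33% | 6/9 = 67% |
| 12 | 6 | 6/12 = 50% | 9/12 = 75% |

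The L = 9 column is shown because 7.10 states 6 months as a minimum. If recruitment closes early on the 10,000-return rule, D shrinks and so does the overlap.

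**4. Effect of a later opportunistic start.** Section 4.1 expects mail-out to begin almost at once and the opportunistic offer to be staggered. Expected returns are about 2,800 by mail-out (9.1.1) and 8,500 opportunistic (9.1.2), so the opportunistic share is 8,500/11,300 = 75%. If the opportunistic offer starts 3 months after entry (an assumed lag) and L = 6:
- D = 9: 0.25 × 3/9 + 0.75 × 0/6 = 8%
- D = 12: 0.25 × 6/12 + 0.75 × 3/9 = 37.5%

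The 33% and 50% above are therefore upper values for L = 6.

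**5. The alternative reading.** If the end of the trial meant the close of the practice's recruitment, the date would be month D − 12. That is between 6 months before entry (D = 6) and entry itself (D = 12), with no self-sampling in it.

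**6. Illustration in percentage points.** The HPV-negative rate is not in the protocol; 80 to 90% is assumed.
- Overdue women: 190,579 × 106/212 = 95,290 (9.1).
- Coverage of about 55 to 63% (section 5) gives a denominator of 95,290/0.45 = 211,754 down the low end of coverage, and 95,290/0.37 = 257,539 at the high end.
- Returns: 10,000 to 11,362, the latter being 106 × 9 × 20 × 0.15 + 8,500.
- Gross contribution: from 10,000 × 0.8/257,539 = 3.1 points to 11,362 × 0.9/211,754 = 4.8 points.
- One third of that is about 1.0 to 1.6 points.

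This treats every negative return as new coverage, although section 7.8.2.1 leaves open whether some of these women would have been screened anyway.

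**The case against.** The best defence is that section 9.2.3 does not mean the 7.10 end. Section 3.2 speaks of a practice-specific end, which a single trial-wide date cannot be. Usage elsewhere is also loose: long-term coverage is set at 13 months after recruitment ends in 4.4, after the trial has ended in 7.8.1.2, and after the last kit in 7.8.2.1. Read as close of recruitment, the date is clean for up to 12 months of recruitment. This shows that the wording is ambiguous, but it does not settle it. Section 9.2.3 gives no such definition, and 7.10 is the only one available.

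It can also be said that section 9.2 leaves detail to the statistical analysis plan. That is fair for what is left open, but this date is fixed here, and an analysis plan that follows it would inherit the problem.

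Three stronger readings are tempting, and the protocol does not support them:
- A reader might infer that the primary coverage endpoint is biased at baseline. Endpoint 2 in section 3.2 starts from practice entry, before any kit, and 9.2.3 keeps that baseline and the monthly series.
- A reader might infer that the reported gain will be too small. Only the self-sampling part of this one contrast shrinks. Section 1 reports falling coverage, and a secular trend could move the observed change either way.
- A reader might take the one-year point to be a seasonal match. The protocol gives no reason for it.

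The possibility of recruiting beyond 12 months ("Potentially, GP practices may recruit for longer if response rates are lower than expected", section 4.2) depends on an approved amendment, so it is a contingency and not the main case.

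**Conclusion.** The point holds, within limits. By the protocol's own definition of trial end, the second baseline in 9.2.3 comes after kits have started at every practice recruiting for more than 6 months: 3 of 9 months in at the average practice and 6 of 12 at the longest, or later if follow-up runs past its minimum. With even accrual and exactly 6 months of follow-up, up to about one third and one half of the self-sampling contribution would drop out of this contrast; a later opportunistic start lowers both. These shares rest on the dates and the accrual pattern. The percentage-point figures also need an assumed HPV-negative rate and are only illustrative. Because the entry baseline and monthly series stay clean, the damage is confined to one additional comparison, but the rule should be corrected before it is applied.

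**What to change.** - In 9.2.3, replace the second baseline date with one that always precedes the practice's first kit mailing or offer. An example is 12 months before that practice closes active recruitment, moved earlier if recruitment is extended beyond 12 months.
- In 3.2 and 9.2.3, define the practice-specific end for coverage as the close of active recruitment at the practice plus the sample-return allowance, and state that it is not the 7.10 trial end.
- Count the 12 months back from the close of recruitment and not from the new end date. With a one-month allowance (section 7.6.3.2 stops analysis one month after the last kit), counting from the end date would give D + 1 − 12 = month 1 at a 12-month practice, again after the start.

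The cost is wording, and possibly a few earlier months in the aggregate NHAIS coverage extract. Monthly practice-level coverage is already planned (9.2.3 and 10.4.1), and nothing changes for participants.

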### 9.2.4 Questionnaire-based sub-study

Descriptive analyses will be carried out in SPSS. Where sample size allows, the distribution of responders across the PAM stages, and the self-reported barriers to previous participation will be

compared across demographic sub-groups (by ethnic group, age, and deprivation). Separate analyses will be carried out for kit completers and non-completers.

## **10 DATA MANAGEMENT**

### **10.1 Data collection tools and source document identification**

#### **10.1.1 Source data**

Source data for the trial will comprise the questionnaire for the sub-study, GP records, laboratory records, hospital records (colposcopy data held in Cyres) and extracts from NHAIS (national screening database).

The questionnaire will be in paper or electronic (via REDCap) format and will be entered into the YouScreen database.

The remaining source data are all in electronic format that will be extracted directly from the original databases.

### **10.2 Data handling and record keeping**

All data transferred between stakeholders, or to KCL will be covered by appropriate data sharing or data processing agreements.

All data provided to or from CFH Docmail will be done so via their HSCN Secure File Transfer (HSCN SFTP). This will include the monthly data extract from CSAS, any ad-hoc repeat kit requests from HSL, and details of undelivered letters or self-sampling kits.

Trial data will be stored securely and made available for audit according to the standard procedures of King's College London. Third party companies will process data on behalf of King's College London including the provider for the Data Safe Haven (DSH) (currently this is AIMES <https://www.aimes.uk/>) and the commercial print company (CFH Docmail).

A YouScreen trial database will be built in RedCap (a secure web application for building and managing online surveys and databases). The RedCap trial database will be kept in a DSH at King's College London. The DSH is a controlled and secured service environment for undertaking research using sensitive data (personal, sensitive-personal, or confidential). The service provides robust controls and safeguards to enable the secure transfer of sensitive data into a highly secure environment where it can be stored, manipulated and analysed by approved members of a research team. Only designated members of the YouScreen trial team will have access to the study database and the Data Safe Haven.

Data transferred/saved in the DSH at King's College London, will be cleaned/queried/checked for missing data.

The final dataset will be exported and analysed in STATA or R: the RedCap database and .csv files will be imported into a statistical programme (e.g. STATA) for final data cleaning and analysis.

### **10.3 Study ID**

The study/participant ID will comprise the encrypted NHS number and will be used to de-personalise the data and to link between seven data sources (see section 10.4). This will enable us to bring together all of the data required for analysis to meet the trial objectives.

For the encryption we plan to use the free open source software OpenPseudonymiser (<https://www.openpseudonymiser.org/Default.aspx>). OpenPseudonymiser allows an encrypted "salt" (an extra string of characters appended to the data being de-personalised) to be added, which ensures that there is no risk of the data being cross referenced by another project that uses different salt. The encryption programme and salt will be created by an individual outside of the King's trial team at Public Health England. The encryption programme and salt will be provided to each of the bodies who will encrypt NHS numbers for the trial. These are: HSL laboratory, participating CCGs and NHS Digital (NHAIS data).

The King's trial team will not have access to the encryption programme at any point and will not be able to decrypt the information. As such, the data held at King's College London will be considered to be effectively anonymous in line with the ICO's anonymisation standard (but will still be stored securely in the DSH).

## **10.4 Datasets**

Trial data will be collected from seven different sources:

- (i) NHAIS database,
- (ii) GP medical records
- (iii) The central NHS laboratory (HSL),
- (iv) Hospital record (colposcopy clinic) data from the Cyres database (Cyres has a central server database where all cytology and histology data from NHS colposcopy clinics in London are uploaded),
- (v) The mailing company (CFH Docmail) and
- (vi) The questionnaire, and
- (vii) Cancer registration data from the National Cancer Registration and Analysis Service.

A further dataset may arise from the analysis of residual samples; however, this will be treated separately from the main dataset (i.e. to be analysed and reported separately). Data arising from the residual samples may be annotated with cancer registration data for future translational research. Linkage to cancer registration data will be conducted using privacy conserving methods as described in 10.3.

The data (csv or excel files) will be uploaded to King's CPTU using a secure electronic transfer method. Once a data file has been downloaded at the King's CPTU and formatted for the YouScreen database by the Data Coordinator or Trial Coordinator it will be uploaded onto the YouScreen database which will be stored in the DSH.

### **10.4.1 NHAIS dataset**

NHAIS holds the national cervical screening database and is therefore, the most accurate and complete source of screening data. GP records also contain cervical screening data, however, this tends to be less accurate than NHAIS as the two systems are not linked. As such, NHAIS data will be the main source of cervical screening data for the trial

Prior to each data extraction NHS Digital will apply the "exclusion" lists to remove women in the national data opt-out and women who have opted out from data usage for the study (see section 7.3.5). NHS Digital will then extract the data and, prior to sending it to KCL, will encrypt the NHS numbers (i.e. generate study ID) and convert the postcode to LSOA. In this way only anonymous line-level data will be provided to the trial team at King's for all eligible women (i.e. ≥6m overdue cervical screening) and therefore, will include data from women who have not consented to the trial. We will seek CAG approval for this. Data will include:

- Study ID (encrypted NHS number)
- Demographic data (age, LSOA (converted from postcode prior to sending to KCL))
- Cervical screening tests (including self-samples, cytology and HPV tests) dates and results, source of self-sample (opportunistic or mailout) including the last test before trial start, all tests during the trial period)
- Date identified for 15m mail out (if applicable)
- Cervical screening disclaimer returned (i.e. opted-out from the cervical screening programme)
- The woman's GP practice

These line-level NHAIS data will be linked to anonymised line-level data from GP records using the study ID to enable us to assess response rates and cervical screening activity according to ethnicity, whether or not women are offered kits in GP primary care.

We will also collect anonymous aggregate data:

- Practice-specific coverage at before study start, monthly and at the end of the trial

- An additional extract on practice-specific coverage may be requested after the trial has ended (after approximately 13 months after the last kit was handed out) to assess long term coverage.

#### **10.4.2 Central Laboratory dataset**

The central laboratory (HSL) will provide detailed data on self-samples that are received at the laboratory for the trial. Although self-sample results will also be obtained from NHAIS, the laboratory will provide critical data on self-samples that will allow us to assess the self-sampling pathway that are not available in NHAIS such as sample received date, analysed date, samples with missing or incorrect information, HPV type, kit ID numbers, and consent status for residual samples (on the lab request/consent form).

The HSL laboratory is the central NHS laboratory for cervical screening in London, therefore have existing permission to receive full PID and will handle data securely to NHS standards.

HSL will encrypt the NHS numbers prior to sending the data to the trial team at King's. De-personalised line-level data will be provided for women who return a self-sample.

Anonymous aggregate data will be collected for:

Number of samples rejected because:

- DNA insufficient (unavailable) –  $\beta$ -globin negative
- Unlabelled sample or missing lab request/consent form
- Damaged in transit
- Identifiers not matched on lab request/consent form and sample tube
- Sample received outside of agreed validity window
- Self-sample already recorded in central laboratory LIMS database
- Woman ineligible for self-sampling because not  $\geq 6$ m overdue cervical screening

#### **10.4.3 Hospital data (colposcopy clinic data from Cyres)**

Cyres is the integrated software that is used by all colposcopy clinics/services in London to generate routine reports (KC65) on referrals to colposcopy, subsequent treatment and outcome, for the cervical screening programme. As the designated London central laboratory for the NHSCSP, HSL are able to access colposcopy data in Cyres for all of London.

HSL will extract any data that are available in Cyres for all women who return a self-sample (downstream events only). Data will include referrals to colposcopy, date of colposcopy, histology date and results of biopsy or treatment (if applicable).

Data will be extracted from Cyres then merged to the main central laboratory dataset using NHS number. HSL will encrypt the NHS numbers (i.e. generate study ID) so that all datasets provided to the King's trial team will be anonymised.

#### **10.4.4 GP record datasets**

Electronic GP record data will provide key data for the trial that are not available from the other data sources, such as ethnicity, granular details of the opportunistic offer (kits offered, accepted and declined, reasons for declining kits, and health professional type offering kits).

Cervical screening (dates and results) data will be obtained to enable us to assess how accurate GP records are for identifying women eligible for the opportunistic offer (it may be that kits may be offered to women who are  $\geq 6$ m according to their GP records but not in NHAIS. Also, cervical screening data in GP records may contain details of tests taken in other countries which are not recorded in NHAIS.

EMIS searches will be written to exclude women who are coded to have opted out from data usage for the study (see section 7.3.5).

GP record data will be extracted in bulk using EMIS searches that have been specially written for the trial. Extracts are likely to be downloaded from participating GP practices once they sign up to the trial (historical cohort data), at the end of the trial and depending on logistics, at several points during the study (e.g. on a monthly basis, at the end of active recruitment). These data extracts will be downloaded centrally at the CCG level by a member of the relevant CCG. If central download is

not possible, it will be carried out by each GP practice by a member of the practice team. The Clinical Effectiveness Group (CEG) have confirmed that they have centralised access to all GP practice data in Tower Hamlets and Newham CCG. Similarly, North East London Commissioning Support Unit (NEL CSU) have access to data from all GP practices in Barnet and Islington CCGs. Camden CCG have an IT lead who we plan to liaise with to extract data for Camden GP practices.

De-personalised line-level data will be collected for all women who are eligible (i.e.  $\geq 6m$  overdue cervical screening) and therefore, will include data from women who have not consented to the trial.

CAG approval will be sought to allow download of identifiable data at the CCG level and to allow the trial team at KCL to access de-personalised line-level data from women who have not consented to the trial. The CCG IT team will encrypt the NHS numbers before securely sending the data to King's.

We plan to use the in-built template and search functions within EMIS web to collect standardised data from GP records. Only anonymous aggregate data or line-level de-personalised data will be accessed by the trial team.

